### **2.1 Study Overview**

The study will be conducted in the Matlab Health and Demographic Surveillance System (HDSS) field area of the International Centre for Diarrhoeal Disease Research, Bangladesh (ICDDR,B) to determine the population effectiveness of Rotarix in Bangladeshi children. Villages in both the Maternal and Child Health and Family Planning intervention area (hereafter referred to as the ICDDR,B service area) and the comparator Government service area will be included in this evaluation. We propose to introduce Rotarix into half of the villages of the Matlab HDSS. In villages randomized to receive the vaccine, all eligible children will be offered Rotarix during their first two Expanded Programme on Immunization (EPI) visits, as would routinely be done if Rotarix were included in the Bangladesh EPI schedule. If a child residing in a village assigned to Rotarix vaccine did not receive Rotarix during the first EPI visit, the child may still receive the Rotarix during subsequent EPI visits so long as the vaccine is given within age guidelines as defined by the Rotarix package insert. In villages randomized not to receive Rotarix, children will receive their EPI vaccinations exactly as they would have in the absence of this study. Administration of Rotarix will be conducted by regular EPI staff, but ICDDR,B study staff will be present to document informed consent and collect study-specific information. The Ministry of Health will be an active partner in this evaluation since they will be the agency which may follow up with any subsequent vaccine programme. Vaccination with Rotarix will be

recorded on the infant's immunization card which is normally used by the EPI programme, but also on a separate study-specific data collection form.

Rotarix vaccination started in the government service area villages in September 2008 (although was not fully operational until November 1 of that year) and in the ICDDR,B service area villages on April 1, 2009. The delayed start in the ICDDR,B service area was to allow for completion of follow-up in the RotaTeq individually-randomized trial which was carried out in the 67 villages of the ICDDR,B service area.

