| According-to-Protocol (ATP) populations for total effectiveness | 
First priority analysis
 
Those included: Infants in the “MITT total effectiveness first priority” population who complete both the second dose of Rotarix and OPV2 (exclusive of birthdose) in Rotarix villages and OPV2 (exclusive of birthdose) in non-Rotarix villages.
 
Follow-up period: Person-time will be counted from date of OPV2 (exclusive of birth dose) plus 2 weeks until two years (731 days) of age or March 31, 2011, whichever comes first.
 
Second priority analysis
 
Those included: Infants in the “MITT total effectiveness second priority” population who complete the second dose of Rotarix in Rotarix villages and all those from non-Rotarix villages.
 
Follow-up period: Person-time will be counted from 26 weeks of age until two years (731 days) of age or March 31, 2011, whichever comes first.
 |
| “Direct effectiveness” populations                       |                                                                                                                                                                                                                                                                                                                                                                                                                                                                                                                                                                                                                                                                                                                                                                                                                                                                                                                                  |

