|                                                                 | 
MITT analysis
 
Those included: Infants in the “overall effectiveness-primary analysis” population from Rotarix villages plus those infants residing in Rotarix study villages who are between 6 and 20 weeks of age on Apr 1, 2009 (ICDDR,B service area) or on Nov 1, 2008 (Govt service area), regardless of receipt of Rotarix.
 
Follow-up period: Person-time will be counted from six weeks of age until two years (731 days) of age or March 31, 2011, whichever comes
                                                                                                                                                                                                                                                                                                                                                                                        |

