|                                             | 
first.
 
ATP analysis
 
Those included: Infants in the “overall effectiveness-primary analysis” population from Rotarix villages plus those infants residing in Rotarix study villages who are between 6 and 20 weeks of age on Apr 1, 2009 (ICDDR,B service area) or on Nov 1, 2008 (Govt service area), regardless of receipt of Rotarix.
 
Follow-up period: Person-time will be counted from 26 weeks of age until two years (731 days) of age or March 31, 2011, whichever comes first.
                                                                                                                                                                                                                                                                                                                                                                                                                                                                                                                                                                                                                                                                                                                                                                                                                                                                                                                                                                                                                                                                                                                                                                                                                         |

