where  $\lambda_0(t)$  is the unspecified baseline hazard function.  $X_i$  does not appear by itself because there is no expected effect of whether a child lives in a Rotarix or control village *per se*, as that was determined through randomization.

The indirect effects at any given level of coverage are estimated by taking the difference of the relevant covariates. For example,  $\exp(\beta_6 - \beta_9)$  gives the relative hazard of those in a highly Rotarix-immunized village compared to those in a highly OPV-only immunized village. Note there will not be a great deal of power for these comparisons, however.

It will also be advisable to add two time-varying dummy variables to track the three main seasons (see the seasonality discussion below).

The best way to analyze these data is to use a gamma frailty model that assigns a random intercept term to each village to account for within-village correlation. Stata has a function for this, although it will take some careful work to split up each child's observation time into a number of intervals to account for all the time-varying covariates. It may also be possible to use the SAS PROC SURVEYPHREG to estimate a robust variance to account for the correlation. The advantage to this approach is that SAS allows for continuously-varying time-varying covariates that are relatively easily coded. If this specification in SAS, that will be the preferred approach for analysis.

*3. To evaluate the direct effectiveness of Rotarix in reducing rates of acute diarrhoea due to rotavirus, as detected by patients admitted to a treatment facility, among vaccinated infants and young children from villages where Rotarix is introduced compared to unvaccinated infants and young children from villages where Rotarix is introduced.*

This direct effect is best estimated by  $\beta_2$  in the above model, which is the remaining effect of Rotarix after accounting for the indirect effects. This will be run for the mITT population.

A second estimate will be provided by applying a Cox model to the Direct effect population (i.e. the mITT population only in Rotarix villages), with a time-varying covariate for receipt of first dose of Rotarix.

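### The direct-effectiveness ATP set is the MITT set with a later start of person-time, and no direct-effect exposure uses the second Rotarix dose

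*SAP*

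**What the plan says.** **Direct effectiveness (SAP section 3.2).** Both sets take the overall-effectiveness primary population from Rotarix villages and add infants there who were 6 to 20 weeks old on the area's start date. Both inclusion rules end "Govt service area), regardless of receipt of Rotarix". The follow-up rules differ:

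- MITT: "Person-time will be counted from six weeks of age until two years (731 days) of age".
- ATP: "Person-time will be counted from 26 weeks of age until two years (731 days) of age".

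**Direct-effect model (SAP section 3.5, secondary aim 3).** The preferred estimate is the coefficient β2 from the model under aim 2. It is the interaction of village type with an indicator that switches on at first OPV, and it is to be run on the mITT population. A second estimate is a Cox model in Rotarix villages "with a time-varying covariate for receipt of first dose of Rotarix", again on the mITT population.

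**Total effectiveness (SAP section 3.2).** Both ATP sets require the second Rotarix dose in Rotarix villages. The first-priority set takes infants "who complete both the second dose of Rotarix and OPV2 (exclusive of birthdose) in Rotarix villages", with the follow-up rule "Person-time will be counted from date of OPV2 (exclusive of birth dose) plus 2 weeks". The second-priority set starts at 26 weeks.

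**Dose timing (SAP section 2.1).** If Rotarix is missed at the first EPI visit, "the child may still receive the Rotarix during subsequent EPI visits so long as the vaccine is given within age guidelines".

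**The concern.** An According-to-Protocol analysis is normally read as the effect once the planned course is complete. The SAP uses the label that way for total effectiveness. For direct effectiveness the same label requires no course completion, either in the population or in the exposure variable.

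A direct ATP estimate computed this way would pool one-dose and two-dose infants as vaccinated. Any difference from the MITT estimate would come from excluding the first months of follow-up, not from completing the course, so a reader could take an age-window effect for a second-dose effect. Because section 3.5 never says which analysis is run on the ATP sets, no later text settles the matter. The SAP says it was written to avoid data dredging, and an unassigned set leaves room for a choice after the results are seen.

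**Working it through.** There is no plan figure to reproduce, because the point rests on definitions. The checks are a comparison of the text and an illustration of size.

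**1. Direct MITT against direct ATP.** The inclusion texts match word for word. The start of person-time moves by 26 − 6 = 20 weeks. The end is the same: 731 days of age or March 31, 2011.

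**2. Use of dose 2 across the definitions.**

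| Definition | Second Rotarix dose used? |
|---|---|
| Total ATP, first priority | Yes, for membership |
| Total ATP, second priority | Yes, for membership |
| Direct ATP set | No |
| β2 (first OPV × village type) | No |
| Second direct estimate (first Rotarix dose) | No |

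**3. Analyses assigned to ATP sets in section 3.5.** Aim 1 uses the overall-effectiveness primary population with a 12-week start, then the mITT population. Aim 3 uses the mITT population. Aims 4 and 5 refer back to the analyses above them. None names an ATP set.

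**4. Size of the dilution in the direct estimate.** Let VE2 be two-dose effectiveness, VE1 one-dose effectiveness and s the share of vaccinated infants with one dose only. With equal underlying risk and similar person-time:

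apparent VE = (1 − s) × VE2 + s × VE1

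VE2 = 50% is assumed, the value that section 2.5 assumes for overall effectiveness. The values of s and VE1 are also assumptions.

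| s | VE1 = 0 | VE1 = 25% | VE1 = 40% |
|---|---|---|---|
| 5% | 47.5% | 48.75% | 49.5% |
| 10% | 45.0% | 47.5% | 49.0% |
| 20% | 40.0% | 45.0% | 48.0% |

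For VE1 of 0–25% the loss runs from 50 − 48.75 = 1.25 points to 50 − 40 = 10 points. If one dose protects almost as well as two (VE1 = 40%), it is 0.5 to 2 points.

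**5. Minor note: the first-priority total ATP clock.** Take a child with Rotarix dose 1 at the OPV2 visit and dose 2 some weeks later. The SAP gives no visit interval. If dose 2 follows OPV2 by 4, 6 or 8 weeks (assumed), the clock at OPV2 + 2 weeks opens 2, 4 or 6 weeks before dose 2. For size, assume a 4-week gap, OPV2 at 10 weeks of age, follow-up to 731 days and no protection until dose 2 + 2 weeks:

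- Affected share of a late child's time: 4 / (731/7 − 12) = 4 / 92.4 = 4.3%.
- With 5% of vaccinees late: 50% × (1 − 0.05 × 0.043) = 49.9%.
- With 20% late: 50% × (1 − 0.20 × 0.043) = 49.6%.

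With a shorter follow-up of about 330 days (assumed), the affected share is 28/330 = 8.5% and the loss is 0.2 to 0.9 points. Either way it is under one point.

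**The case against.** **The quoted phrase is not itself a mistake.** A reader might infer that infants without Rotarix should be removed from the direct ATP set. Aim 3 compares vaccinated with unvaccinated infants inside Rotarix villages, so zero-dose infants must stay. This objection stands. The gap is the missing distinction between one and two doses.

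**Course completion is required elsewhere.** A reader might infer that none of the ATP definitions demands the full course. Section 3.2 does not support that, since both total-effectiveness ATP sets require dose 2 for membership. Only the first-priority clock is open to question, and no fault is shown for the set that starts at 26 weeks.

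**No exposure is stated for the direct ATP set.** The SAP ties both direct-effect exposures to the mITT population, so counting one-dose infants as vaccinated in the ATP set is a carry-over. That is correct, and the dilution figures are conditional on it. It does not rescue the definition: neither stated exposure uses dose 2, and section 3.5 supplies no other.

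**The estimate is imprecise anyway.** Section 3.5 expects over 90% coverage. Take 5,825 infants per group and a 3.5% attack rate (section 2.5), and assume exactly 90% coverage, 50% direct effectiveness and no indirect effect:

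- Unvaccinated cases: 5,825 × 0.10 × 0.035 = 20.4.
- Vaccinated cases: 5,825 × 0.90 × 0.0175 = 91.7.
- SE of the log rate ratio: √(1/20.4 + 1/91.7) = 0.245.
- 95% interval for the rate ratio: 0.5 × exp(±1.96 × 0.245) = 0.31 to 0.81, so effectiveness of 19% to 69%.

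This makes no allowance for clustering, and a 26-week start would widen it. A shift of 1 to 10 points lies well inside it. That limits the practical weight of the point but does not make the label correct.

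**The SAP never proposes reading ATP minus MITT as the gain from the second dose.** This is also true. Even after the fix, that contrast would remain open to age-window and selection effects.

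**Conclusion.** The point holds for the direct-effectiveness ATP analysis. As written it cannot estimate a completed-course effect. It repeats the MITT comparison from 26 weeks of age and, with either exposure in section 3.5, counts one-dose infants as vaccinated.

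The dilution is about 1 to 10 points, resting on assumed 50% two-dose effectiveness, 5–20% one-dose infants and 0–25% one-dose effectiveness. It would be smaller if one dose protects nearly as well as two. One-dose infants may also differ in underlying risk, so the direction is less certain than the formula suggests.

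The first-priority total ATP clock is a minor matter. It can open before dose 2 only for children whose Rotarix doses lag their OPV doses, and it is worth under one point on the assumed shares. A reader might infer that the total ATP results are materially biased; the documents give no basis for that.

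These are secondary analyses, and the primary overall-effectiveness analysis is unaffected. The definition should still be settled before unblinded results are seen.

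**What to change.** For direct effectiveness:

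- In section 3.2, keep zero-dose infants in Rotarix villages as the comparator.
- Define ATP exposure as two recorded Rotarix doses, the second at least 2 weeks before person-time starts at 26 weeks. Both margins are already in the SAP, and exposure is then fixed when the clock opens.
- Exclude one-dose infants or report them as a separate category. Say how infants whose second dose falls after that cut-off are handled; the same separate category would serve.
- In section 3.5, aim 3, state that the Cox analysis in Rotarix villages is run on the direct ATP set with this exposure.

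For the first-priority total ATP set, keep the OPV2 clock, which is common to both arms, and add a sensitivity analysis for children whose second Rotarix dose came after OPV2. Requiring dose 2 by OPV2 would remove late starters from Rotarix villages only, with no matching exclusion in the comparison villages.

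The cost is a few lines of SAP text and a derived variable from vaccinations already recorded on the immunization card and study form (section 2.1). Some infants leave the direct ATP comparison, and the estimate stays imprecise because few infants are unvaccinated. No vaccination procedure changes.

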|                                             | 
Three groups are definable for analysis of indirect effects.
 
Indirect Population 1
 
Those included: Infant and child residents of Matlab who are at least 20 weeks of age as of Apr 1, 2009 (ICDDR,B service area villages) or Nov 1, 2008 (Govt service area villages) or in-migrants to the study area who are between 20 weeks and 2 years of age during the study period. Treatment group assignment for these children will be determined by village of residency at the time that first allows them to be included in this population.
 
Follow-up period: Person-time will be counted from Apr 1, 2009 (ICDDR,B service area villages) or Nov 1, 2008 (Govt service area villages) or date of in-migration until two years of age (731 days) of age or March 31, 2011, whichever comes first.
 
Indirect Population 2
 
Those included: Infants who resided in Matlab between 6 and 20 weeks of age after Apr 1, 2009 (ICDDR,B service area) or after Nov 1, 2008 (Govt service area).
 
Follow-up period: Person-time will be counted from Apr 1, 2009 (ICDDR,B service area villages) or Nov 1, 2008 (Govt service area villages) or date of in-migration until receipt of OPV1, the child turns two years of age (731 days), or March 31, 2011, whichever comes first.
 
Indirect Population 3
 
Those included: All infants or children resident of the study area aged between 6 weeks and 2 years at some point during the study period.
 
Follow-up period: All person-time contributed during the study period. The analysis will account for receipt of vaccine (this will include any
 |

|  |                                                                                                |
|--|------------------------------------------------------------------------------------------------|
|  | indirect effects that also accrue to those who receive Rotarix, which is not 100% protective). |
|--|------------------------------------------------------------------------------------------------|

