### *Primary Aim*

*To evaluate the population (overall) (Halloran, et al., 1997) effectiveness of Rotarix in reducing rates of acute diarrhoea due to rotavirus, as detected by patients admitted to a study treatment facility, among all infants and young children from villages where Rotarix is introduced compared to among those from villages where Rotarix is not introduced.*

Main analysis, on Overall population: first episodes of rotavirus diarrhea. A Poisson regression with Pearson scale parameter (calculated at the village level) will be fit, offset with person-years of exposure, with a dummy covariate for village randomization arm status and a dummy covariate for villages in the Matlab service area (corresponding to the stratified randomization).

Note that this overall effectiveness is a function of vaccine efficacy and vaccine coverage. Since over 90% coverage is expected, this will not be much different from a total effects analysis. Also, if there are any indirect effects that act to reduce transmission, these may exert a differential effect over time, as it is not until near the end of the study period that the entire population of children under 2 years of age will be saturated with vaccine.

Additional analysis: same as main analysis, but including **all** episodes of rotavirus diarrhea, not just first episodes. The scale parameter at the randomization unit level also accounts for all within-child correlation, so the same analysis approach can be used.

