### *Secondary Aims*

*1. To evaluate the total effectiveness of Rotarix in reducing rates of acute diarrhoea due to rotavirus, as detected by patients admitted to a study treatment facility, among vaccinated infants and young children from villages where Rotarix is introduced compared to unvaccinated infants and young children from villages where Rotarix is not introduced.*

Main analysis, “overall effectiveness” primary analysis population: with the modification of starting observation time at 12 weeks instead of 6 weeks of age. A Poisson regression with Pearson scale parameter (calculated at the village level) will be fit, offset with person-years of exposure, with a dummy covariate for village randomization arm status and a dummy covariate for villages in the Matlab service area.

Additional analyses:

- a. As in 1., but for all (not just first) cases of rotavirus diarrhea.
- b. As in 1. and 1.a, but for the mITT population.

*2. To evaluate the indirect effectiveness of Rotarix in reducing rates of acute diarrhoea due to rotavirus, as detected by patients admitted to a study treatment facility, among unvaccinated*

*infants and young children from villages where Rotarix is introduced compared to those from villages where Rotarix is not introduced.*

*Analyses are given according to the populations a, b, c given above.*

a) Those aged at least 20 weeks as of Nov 1, 2008 (Apr 1, 2009), with censoring at earliest of 2 years of age or Mar 31, 2001, whichever comes first. Also included are those who in-migrate between ages 20 weeks-2 years. Poisson regression as described above will be used; all cases (first and subsequent) will be used.

b) Those in the Overall population, but with censoring at first OPV dose. Because of the high coverage, this will not comprise many person-years. Poisson regression as described above will be used; all cases (first and subsequent) will be used.

c) All person-time contributed by infants or children who were between 6 weeks and 2 years of age at some point during the study period.

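### Aim 2(a) fits one constant arm effect to Indirect Population 1, whose launch residents are seen almost only during Rotarix roll-out, so the pooled result is a roll-out average and should be labelled and split by time

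*SAP*

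**What the plan says.** **Population.** SAP Section 3.2 defines Indirect Population 1 as "Infant and child residents of Matlab who are at least 20 weeks of age as of Apr 1, 2009 (ICDDR,B service area villages", with 1 November 2008 as the matching date for the government area. It adds "in-migrants to the study area who are between 20 weeks and 2 years of age during the study period". Person-time runs from the launch date "or date of in-migration until two years of age (731 days) of age or March 31, 2011, whichever comes first". (Aim 2(a) in Section 3.5 prints the closing year as 2001. I take this as a slip and use the 2011 date of Section 3.2.)

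**Model.** Section 3.5, Secondary Aim 2(a), states: "Poisson regression as described above will be used; all cases (first and subsequent) will be used". The model referred to is that of the Primary Aim, a Poisson regression offset by person-years "with a dummy covariate for village randomization arm status and a dummy covariate for villages in the Matlab service area". It has no term for calendar time, time since launch or coverage.

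**The SAP's own remark on timing.** Under the Primary Aim it says that indirect effects may act differently over time, since "it is not until near the end of the study period that the entire population of children under 2 years of age will be saturated". Expected coverage is over 90%: "Since over 90% coverage is expected, this will not be much different from a total effects analysis".

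**Other analyses of the indirect aim.** Aim 2(b) censors at the first OPV dose, and the SAP expects it to hold few person-years. Aim 2(c) is a Cox model with time-varying arm-by-coverage categories, for which the SAP expects limited power. Its village coverage is the share of children aged 6 weeks to 2 years with at least one OPV dose, and its individual vaccination indicator switches on at the first OPV dose.

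**The concern.** Indirect protection of children too old to be vaccinated depends on how many of the children around them have received Rotarix. At launch that share is near zero, and it rises only as vaccinated birth cohorts replace older ones. Launch residents leave follow-up over the same months, so most of their person-time comes early, when there is little vaccine in the village. One arm coefficient averages over all of it.

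The SAP acknowledges the mechanism under the Primary Aim and then applies a constant effect in Aim 2(a). Nothing labels the result as an average over roll-out. The SAP says that its analyses are to inform policy. A small or null pooled estimate could therefore be taken as absence of herd protection from a programme with over 90% coverage, when it mainly describes the first year after launch.

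**Working it through.** The SAP states no figure for Aim 2(a) or Indirect Population 1. Its sample size concerns the primary aim only (77 × 3.48 = 268 admissions; 268 / (0.035 × 0.75) = 10,210 infants). It reproduces and has no bearing here.

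**Inputs from the SAP**
- Minimum age of launch residents: 20 weeks = 140 days. Follow-up ends at 731 days or 31 March 2011.
- Launch: 1 November 2008 (government), 1 April 2009 (ICDDR,B).
- Coverage plateau: 0.90, from the expectation of over 90%.
- Infants aged 6 to 20 weeks at launch are counted in some analysis populations, so catch-up vaccination is plausible.

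**Assumptions, not in the SAP:** uniform ages, steady births, 90% uptake at 6 weeks, coverage counted among children aged 42 to 731 days, and zero coverage on the launch date. Section 2.1 says that government-area vaccination began in September 2008, so coverage there may have been somewhat above zero.

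**1. When launch residents leave.** Maximum follow-up is 731 − 140 = 591 days. Launch + 591 days is 15 June 2010 (government) and 13 November 2010 (ICDDR,B). To 31 March 2011 there remain 289 days (41 weeks) and 138 days (20 weeks).

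**2. Distribution of their person-time.** On day *t* the number still followed is proportional to 591 − *t*. Mean *t* is 591/3 = 197 days. The share of person-time after day *t* is ((591 − *t*)/591)².

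**3. Rotarix coverage on day *t*.** The age window is 731 − 42 = 689 days.
- No catch-up: *c* = 0.90 × *t*/689. Mean = 0.90 × 197/689 = 0.257.
- Full catch-up of the 6–20 week group (98 days of births): *c* = 0.90 × (*t* + 98)/689. Mean = 0.90 × 295/689 = 0.385.

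Weighting by the age-specific admission rates in Section 2.5 instead of person-time gives 0.246 and 0.374.

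| Launch residents | No catch-up | Full catch-up |
|---|---|---|
| Mean coverage | 0.257 | 0.385 |
| Person-time at coverage below 25% | 54% | 29% |
| Person-time at coverage of 75% or more | 0.1% | 4% |
| 0.90 / mean coverage | 3.5 | 2.3 |

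With admission-rate weighting the last row becomes 3.7 and 2.4.

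**4. In-migrants.** The SAP gives no number. With an assumed 2% to 15% per year, the ratio of plateau to mean coverage is 2.0 to 2.35 with catch-up and 2.7 to 3.5 without.

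**5. From coverage to effect.** If the indirect effect is proportional to coverage, these ratios are the factor of understatement, about 2 to 3.7. An assumed 30% effect at the plateau would then average 30% × 0.257/0.90 = 8.6% to 30% × 0.385/0.90 = 12.8% in residents. If the effect follows the square root of coverage the factor is about 1.6 to 2.1; if it follows the square, about 4.1 to 8.7.

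**6. Season.** The SAP gives no monthly rates, so season is not weighted above. As a limiting case, suppose that all cases fall in November to February.
- Government residents: winters are days 0–120 and 365–485, with person-time 63,720 and 19,920 units, so 76% falls in the first winter. Mean *t* is 143.5, and coverage is 0.19 (no catch-up) or 0.32 (catch-up).
- ICDDR,B residents: essentially one winter, days 214–334. Mean *t* is 270, and coverage is 0.35 or 0.48.

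Season therefore moves the two areas in opposite directions. The proportional factor would run from 0.90/0.48 = 1.9 to 0.90/0.19, about 4.8, inside the overall range of 1.6 to 8.7.

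**7. Whether Aim 2(c) fills the gap.** Read literally, its coverage counts OPV doses given before launch. A village could then sit in a high-coverage category on day one with no Rotarix given. Its vaccination indicator would be 1 for an older child with earlier OPV, and in a Rotarix village the interaction term would code that never-eligible child as Rotarix-vaccinated. The categories would not track roll-out.

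**The case against.** The strongest case on the other side has five parts.

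- **The population is not confined to roll-out.** In-migrants aged 20 weeks to 2 years may enter at any time and be followed to 31 March 2011. This stands. The timing argument applies to launch residents, and the in-migrant share is unknown.
- **Dilution needs a target.** Aim 2 compares unvaccinated children between arms and names no coverage level. The pooled contrast follows the randomisation and is a legitimate average over roll-out. This stands. A reader might infer that Aim 2(a) is biased, or that it claims to measure the effect at saturation, but the SAP makes no such claim.
- **The factor is assumed.** A reader might also infer a fixed two- to three-fold dilution. The document does not support one, because the size depends on the shape of the coverage effect, the extent of catch-up and in-migration. This stands.
- **The SAP already plans a coverage-specific analysis.** Aim 2(c) has coverage categories and adjusts for individual vaccination, so the presence of vaccinated children is not in itself a defect. The SAP also does not rank 2(a) above 2(c). This stands only in part, because the OPV-based definitions leave it unclear whether 2(c) describes Rotarix coverage at all.
- **Replacing the arm term by village Rotarix coverage has a cost.** Uptake arises after randomisation and may go with care-seeking. This stands, and such a model should not be the main one.

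**Conclusion.** The point holds in a limited form. The dates are firm: launch residents have at most 591 days and are gone 41 and 20 weeks before the study ends. So is the model: Aim 2(a) has one constant arm effect, despite the SAP's own statement that indirect effects may vary over time.

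The coverage figures (mean 0.26 to 0.39 against 0.90) rest on uniform ages, 90% uptake and cohort replacement. If the indirect effect grows with coverage, the pooled estimate understates the effect at high coverage. How far is a matter of assumption.

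This concerns one of three analyses of a secondary aim and does not touch the primary analysis. It is a matter of interpretation and reporting, and a cheap improvement.

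**What to change.** In Section 3.5, Aim 2(a):

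1. Keep the pooled randomised arm contrast. Label it a roll-out average, and report with it the person-time-weighted mean Rotarix coverage in Rotarix villages and the share of person-time from in-migrants.
2. Split person-time by time since area launch, add period terms to the Poisson model, and report arm contrasts by period, for example 0–26, 27–52 and over 52 weeks.
3. Treat any model of arm by village Rotarix coverage as supportive only.
4. Do not rely on Aim 2(c) for the effect at a given coverage level while its coverage and vaccination variables count OPV doses given before launch. Define both from doses given after launch.

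**Cost.** Wording and data splitting of a kind that Aim 2(c) already requires; no new data. The drawback is wide intervals in later periods. Under the assumptions above, the three periods hold about 52%, 33% and 15% of residents' person-time, from 1 − (409/591)² = 0.52 and (227/591)² = 0.15. In the last period mean *t* is 364 + 227/3 = 439.7 days, so mean coverage is 0.90 × 439.7/689 = 0.57 without catch-up and 0.90 × 537.7/689 = 0.70 with it. Even that period falls short of the plateau for residents.
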